**Fig. 1 Fig1:**
[figure not shown]
Flowchart for the work plan and data collection

### Randomization and blinding

Recruited, eligible participants will be randomized into two groups (1:1 ratio), using random numbers table generated in the Statistical Package for Social Studies (SPSS v. 21) (SPSS v. 21, IBM Corp., New York, NY, USA) by an independent statistician. The laboratory staff, biostatistician, health educator, and principal investigator will be blinded to the participant’s group allocation until the end of the study. The participants will not be blinded to the intervention due to its nature, as well as the research assistant/project manager who is responsible for disseminating the text message intervention.

### Baseline visit

#### Lifestyle education

Eligible prediabetic subjects from the previous HHP study [20] will be invited to the HHP office. If they give consent for this trial, then participants will be assigned to either the intervention or the control group by the computer-generated list. At this baseline visit, all participants will receive group education and motivation about lifestyle modifications along with written information about diet and physical activity recommendations offered by a diabetic educator and a physician. This will advise participants on balancing food intake and physical activity to achieve and maintain appropriate body weight. All participants will take Metformin 500 mg twice daily. In addition, only participants in the intervention group will receive SMS messages at frequent intervals. These messages will be about a healthy lifestyle, the benefits of physical activity and a healthy diet. Neither group will receive any additional lifestyle information or advice by personal contact after the baseline visit, except in response to specific queries from the participants.

#### Physical measurements

At the baseline visit, all recruited participants’ weight, height, waist circumference, and blood pressure from the left arm will be measured in a sitting position, and the mean of two readings will be considered. Blood tests for HbA1c and lipid profiles will be performed by qualified laboratory personnel. Glycated hemoglobin (HbA1c) and fasting lipid profiles will be measured for all participants at baseline and at every 6-month follow-up visit.

#### Assessment of interventions

All participants will complete the WHO STEPS instrument version 3.1 at the baseline visit and during each follow-up visit. This will assess behavioral risk factors including healthy diet, physical activity and the participants’ behavioral change(s) stage based on the TTM at the baseline visit and follow-up visits for progression in the stages of change.

Data about adherence to physical activity and healthy dietary intake recommendations will be recorded at every 6-monthly follow-up visit. Adherence will be self-reported every 6 months and scored as poor, moderate or good. Physical activity and dietary intake will be categorized as adherent or nonadherent for statistical analysis.

At every visit after the baseline visit, we will assess the mobile messages in the intervention group through a specially designed questionnaire. It will assess the user acceptability and satisfaction of the SMS messages program using a scoring system of 0–10. It will assess message content, frequency, clarity, effect on personal life (“degree of disturbance”), and personal views of the impact of these messages on lifestyle. The list of questions also includes the preferred time to receive messages and invites suggestions for improvement. A maximum total score of 10 denotes that the text messages were highly acceptable and satisfactory, while the lowest score of zero denotes that the text messages were the least acceptable and unsatisfactory.

#### Six-monthly follow-up visits

Subjects will be given appointments for follow-up visits at the baseline visit, 6, 12, 18, 24 and 30 months, a total of six visits plus the baseline visit. Therefore, all subjects will repeat steps 1–3 of the first 6-month follow-up visit, at each of these visits as shown in the flowchart (Fig. 1).

### Definitions and measurements

#### Definitions of cardiometabolic risk factors

##### **Prediabetes** [Impaired glucose tolerance (IGT) and impaired fasting glucose (IFG) [33, 34]]

Subjects will be defined as prediabetic, if the level of glycated hemoglobin (HbA1c) is 5.7–6.4% as per WHO and American Diabetes Association (ADA) criteria [35], or the subject was previously diagnosed as prediabetic.

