## Background

Impaired glucose tolerance (IGT) and impaired fasting glucose (IFG) are intermediate conditions sometimes called prediabetes, where blood glucose levels are above normal but below diabetic thresholds [1]. Seventy percent of individuals with prediabetes eventually develop type 2 diabetes mellitus (T2DM) [2]. While people with IFG have a 20–30% chance of developing diabetes over the course of 5–10 years [3–5], this chance escalates to 90% if the individual is diagnosed with IGT [6]. In Saudi Arabia, the prevalence of both prediabetes and T2DM is high (18.3 and 11.9%, respectively) and increases with age [7]. Even though T2DM is treatable, it is usually associated with other comorbidities such as hypertension, hypercholesterolemia and obesity. These conditions in patients with T2DM contribute to the development of cardiovascular diseases (CVD). Thus, T2DM is one of the modifiable risk factors that can decrease the risk of several chronic diseases such as CVD, and reduce its associated mortalities. A population-based study from England showed that prediabetes may convert back to normal glycemia [8]. Furthermore, landmark clinical trials have proven the effectiveness of lifestyle interventions towards a healthy diet and sufficient physical activity to reduce or delay the occurrence of T2DM by 50% in prediabetic individuals [9–11]. The Center For Disease Control and Prevention (CDC), and the American College of Sports Medicine have demonstrated that accumulation of 10,000 steps per day on most days of the week is an important component of improving glycemic control, insulin sensitivity, and/or cardiovascular (CV) risk in patients with T2DM [1, 12].

Targeting this at risk population of prediabetics and increasing their awareness about the importance of a healthy lifestyle will help in the long run, to significantly decrease the prevalence of T2DM in Saudi Arabia. While many educational programs have been used to promote health in the Saudi community, the use of a digital approach is still in its early stages [7]. Nowadays, the daily use of smartphones is vital due to their efficiency, connectivity and functionality. This makes the delivery of educational messages easier and more convenient.

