## Methods/design

### Study design (setting, eligibility and recruitment)

This is a three-year randomized controlled trial that includes Saudis ≥18 years of age. Participants for the present study will be recruited from the Heart Health Promotion study (HHP), which was conducted at King Saud University from 8 July, 2013 to 30 April, 2014 [20]. In the HHP study, participants were recruited from the three primary health care clinics serving the employees and their families at King Khalid University Hospital [20]. The HHP study was conducted on a large group of Saudi adults, who were at a higher risk of developing T2DM within 2–3 years. Recent data record updates of the original study on May 2017, revealed that out of the total sample (1234 prediabetic subjects) enrolled in the HHP study, 218 individuals had developed overt diabetes during the last 4 years (May 2013–May 2017). Therefore, 1016 are eligible for the present study.

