### Inclusion criteria

The inclusion criteria for participants is Saudi adults aged ≥18 years, literate, prediabetic, with no contraindication of physical activity, have a smartphone with easy access to the internet and are willing and able to provide written informed consent to participate in the study.

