### Recruitment

Recruitment will take place over a 2-month period in order to ensure that all eligible subjects (from the HHP study) who fulfil the inclusion criteria are invited, give consent, and are enrolled following the steps of the baseline visits as shown in the flowchart (Fig. 1). The research team’s database has a contact list and they will recruit individuals over 6–8 weeks. Subsequently, they will be given a 6-month follow-up visit appointment.

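### A 2013–14 diagnosis is enough to count as prediabetic, so people whose HbA1c is now below 5.7% can be randomised and given metformin

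*Protocol article*

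**What the plan says.** *Inclusion criteria* asks for "Saudi adults aged ≥18 years, literate, prediabetic, with no contraindication of physical activity". The prediabetes entry under *Definitions of cardiometabolic risk factors* gives two routes to that label: HbA1c of 5.7–6.4%, "or the subject was previously diagnosed as prediabetic". The second route carries no time limit and no confirmatory test.

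*Study design* draws all candidates from 1234 prediabetic HHP subjects (8 July 2013 to 30 April 2014). It removes the 218 who had become diabetic by May 2017 and concludes: "Therefore, 1016 are eligible for the present study". *Exclusion criteria* rules out people with diabetes and sets no lower glycaemic limit.

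At the baseline visit, *Lifestyle education* says: "If they give consent for this trial, then participants will be assigned to either the intervention or the control group". It adds: "All participants will take Metformin 500 mg twice daily". *Physical measurements* lists the tests for recruited participants: "Blood tests for HbA1c and lipid profiles will be performed by qualified laboratory personnel". The text presents HbA1c there as a baseline measurement and not as a condition of entry. The *Background* accepts that "prediabetes may convert back to normal glycemia".

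**The concern.** Because the two routes are joined by *or*, and the whole recruitment pool already meets the second, the HbA1c range excludes nobody at its lower end. The pool was cleaned in one direction only: people who progressed to diabetes were taken out, and people who reverted to normal were not.

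Two things are at stake. First, participants outside the only glycaemic range the article states would take a glucose-lowering drug, in both arms. Second, the *Primary objective* concerns people with impaired glucose tolerance (IGT), and someone now normoglycaemic is not in that group. Such people also start further from the HbA1c threshold of 6.5% that defines diabetes, so they may contribute fewer events.

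**Working it through.** **1. The plan's own count.** 1234 − 218 = 1016, which matches *Study design*. The subtraction contains no term for reversion. If R of the 1234 have reverted and none of them is among the 218, their share rises from R/1234 to R/1016, a factor of 1234/1016 = 1.21.

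**2. Age of the qualifying diagnosis.**
- At the May 2017 record update: from 30 April 2014 to 1 May 2017 is 3.0 years; from 8 July 2013 to 31 May 2017 is 3.9 years.
- At registration on 4 June 2018: 4.1 to 4.9 years.

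**3. A candidate with HbA1c below 5.7% today, taken through the text.**
- Prediabetic criterion: met through the earlier diagnosis.
- Remaining inclusion criteria (age, literacy, smartphone, consent, fitness for activity): unrelated to glycaemia.
- Exclusion for diabetes: not triggered.
- Baseline visit: consent, assignment, metformin.

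Nothing in the text turns this person away. Fig. 1 is not shown and may place the blood test before allocation. Even so, a low result would not make the person ineligible under the stated definition.

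**4. How many people.** The documents give no share s now below 5.7%. With s assumed to be 10–40%:
- affected among the 300 in *Sample size calculation*: 300 × s = 30 to 120;
- left in the pool if the range were enforced: 1016 × (1 − s) = about 914 to 610;
- people to test to find 300 in range: 300/(1 − s) = about 333 to 500, or 33 to 200 more than 300, before other exclusions and refusals.

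**5. Room in the pool.** 1016 − 300 = 716, so 716/1016 = 70% could be lost for any reason before fewer than 300 remain.

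**6. Does the planned event rate suffer?** In the HHP cohort 218/1234 = 17.7% became diabetic over 4 years. At constant hazard that is −ln(1 − 0.177)/4 = 0.049 per year, or a 2-year risk of 1 − exp(−2 × 0.049) = about 9.3%. *Sample size calculation* assumes 10% over 2 years in the control group. The cohort behind the 9.3% was not purged of reverters, so it gives no evidence of a shortfall against the plan.

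**The case against.** **The old diagnosis is only one criterion.** This is correct. It settles the prediabetic criterion and nothing else, and a reader should not infer that it secures entry by itself.

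**Eligibility may be settled before assignment.** *Recruitment* speaks of people "who fulfil the inclusion criteria are invited, give consent, and are enrolled", *Randomization and blinding* refers to eligible participants, and excluding diabetes at HbA1c 6.5% or above plausibly needs a current result. A condensed article may also leave the order of steps to its flowchart. All of this stands, so no weight is placed on a missing screening sequence. The problem is the definition, which a low result would still satisfy.

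**The history route has a purpose.** IGT and impaired fasting glucose (IFG) are defined by glucose, and a person with either can have HbA1c below 5.7%. This also stands: not everyone below 5.7% has reverted, and a rule based on HbA1c alone would lose some of the intended population. It does not justify accepting a diagnosis more than four years old at registration with no current test of any kind.

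**Stronger readings that the documents do not support.**
- A reader might infer a quantified loss of events. With relative conversion rate r among those below 5.7%, the loss is s × (1 − r): 5% at s = 10% and r = 0.5, and 40% at s = 40% and r = 0. Both inputs are assumed, and the comparator (300 people all in range) is not one the plan uses.
- A reader might infer that the 10% control rate is too high. The 9.3% above does not show this. The article does not say where its 10% comes from, and those still free of diabetes in 2017 may differ from the full cohort.
- A reader might infer bias between arms. The entry rule applies before randomisation and metformin goes to both arms, so the contrast is not biased.

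**Conclusion.** The concern holds in limited form and is worth fixing. As written, a person whose only qualification as prediabetic is an HHP diagnosis from 2013–14 can be randomised and given metformin with a current HbA1c below 5.7%, provided the other criteria are met. The consequences are avoidable drug exposure and a population that partly misses the trial's question. The number affected is unknown, and the 30–120 of 300 rests entirely on the assumed 10–40%. An effect on the number of diabetes events is possible but cannot be sized from the documents. The validity of the randomised comparison is not in doubt. Confidence is moderate, because the share is unknown and the flowchart is not shown.

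**What to change.** 1. Use the previous diagnosis only to identify whom to invite, and delete it as a sufficient route in the prediabetes definition.
2. Require the HbA1c already planned at baseline to be 5.7–6.4%, with the result back before allocation and before metformin is started. Excluding current diabetes already calls for a current value, so this adds the lower bound to the same check.
3. Optionally, admit people below 5.7% on a current fasting glucose in a stated IFG range. Fasting glucose is already needed for the *Metabolic syndrome* definition, so no glucose tolerance test has to be added.
4. Describe the 1016 as the pool to be screened, not as eligible.

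The cost is a short delay between blood draw and allocation (a second contact or a result-first visit), some extra HbA1c tests (33–200 at the assumed shares) and a short ethics amendment. The pool becomes smaller. That is manageable against a target of 300, but the 1016 recruits named in the abstract could not all be enrolled. Some people with isolated IGT and HbA1c below 5.7% would be lost even with the fasting glucose route. The sponsor should state that it accepts this loss.

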### Diabetes mellitus

Diabetes mellitus will be defined as per WHO and ADA criteria of HbA1c level ≥ 6.5% or the subject being previously diagnosed as diabetic and using anti-diabetes medication [35].

### Dyslipidemia

Subjects will be categorized as having any sort of dyslipidemia according to the WHO and the Third Adult Treatment Panel (ATP-III) of the National Cholesterol Education Program (NCEP). Dyslipidemia includes raised levels of total cholesterol, and/or low-density lipoprotein cholesterol (LDL-C), and/or triglycerides and low levels of high-density lipoprotein cholesterol (HDL-C), or if the subject reported using medications to lower blood lipid levels [36, 37].

### Metabolic syndrome (MetS)

Participants will be identified as having MetS using the NCEP-ATPIII criteria, if the subject has at least three out of five factors including abdominal obesity, dyslipidemia (raised triglycerides and reduced HDL-C), raised fasting plasma glucose and hypertension [38].

### Physical activity

Participants will be identified as physically active if they achieve 150 min per week (at least 5 days per week) of moderate activity such as brisk walking or 1 hour of vigorous activity [39]. Furthermore, in the current study, we will measure their achieved steps per week, considered in the 1st week of each 6-month follow-up visit using a pedometer through health applications in the smartphones to count steps.

### Measurements of physical activity adherence

Physical activity adherence was classified into three. Poor**:** Less than 150 min/week of moderate activity or 1 hour of vigorous activity (non-adherent). Fair: About 150–250 min/week of moderate activity or 1 h, 130 min of vigorous activity (adherent).

Good: More than 250 min/week of moderate activity, or if work involved, vigorous work (adherent).

### Healthy eating

Healthy eating such as following the food pyramid and encouraging participants to consume the recommended portions of fruit and vegetables and avoiding unhealthy dietary habits, according to the WHO recommendations for a healthy diet [40]. This includes avoiding fast food, fatty food, sugar-sweetened beverages and refined carbohydrates, decreasing salt intake (< 5 g/day equivalent to sodium intake of < 2 g per day), encouraging more fiber-rich food intake such as whole grains and legumes, and avoiding late night snacks.

### Measurements of dietary adherence

Dietary adherence is divided into three categories: Poor: Not following the advice for more than five servings/day/week (non-adherent). Fair: Occasional deviation from following advice for 2–4 servings/day/week (adherent). Good: Strictly following diet advice for more than 5 servings/day/week (adherent).

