#### Primary outcome

Adoption of healthy lifestyle behaviors including healthy eating and physical activity practices complying with WHO recommendations. Incidence of T2DM, based on a change in HbA1c with an expected reduction of 1–2% at the end of the trial.

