#### Secondary outcomes at 6-month follow-up visits

Change in the TTM towards stages of action and maintenance, decreased levels of LDL-C to < 130 mg/dl or ≤ 5.1 mmol/l, change in the systolic\diastolic blood pressure to normal blood pressure < 120/80 mmHg, respectively, decrease in body weight by 5–10% per year, improvement in the physical activity level to the recommended 150 min per week and improvement in the daily consumption of portions of fruit and vegetables to 5–7 servings/day.

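### The diet and physical activity adherence rules cannot be applied as written, and on the reading that fits its top class the diet rule conflicts with the plan's own servings target

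*Protocol article*

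**What the plan says.** **Use in analysis.** Under Assessment of interventions, adherence is self-reported every 6 months on a three-level score, and then: "Physical activity and dietary intake will be categorized as adherent or nonadherent for statistical analysis". The middle level is called moderate there and Fair in the two adherence sections.

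**Diet** (Measurements of dietary adherence), from the highest class down:
- The top class is worded as "Good: Strictly following diet advice for more than 5 servings/day/week (adherent".
- The class below it, also counted as a success, is worded as "Fair: Occasional deviation from following advice for 2–4 servings/day/week (adherent".
- The lowest class, the only one counted as a failure, is worded as "Poor: Not following the advice for more than five servings/day/week (non-adherent".

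**Diet target** (Secondary outcomes at 6-month follow-up visits): "improvement in the daily consumption of portions of fruit and vegetables to 5–7 servings/day".

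**Activity** (Measurements of physical activity adherence):
- Poor, non-adherent: under 150 min/week moderate, or one hour vigorous.
- Fair, adherent: about 150–250 min/week moderate, "or 1 h, 130 min of vigorous activity (adherent".
- Good, adherent: over 250 min/week moderate, or vigorous work.

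The separate section Physical activity counts a person as active at 150 min/week of moderate activity, on at least 5 days, or at one hour of vigorous activity.

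**Primary outcome.** The behaviour component reads "Adoption of healthy lifestyle behaviors including healthy eating and physical activity practices complying with WHO recommendations". It gives no cut-off and does not mention the adherence classes.

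**The concern.** A binary analysis variable needs a rule that places every participant in exactly one class. These rules do not, so whoever derives the variable must choose a unit, settle the overlaps and fill the gaps, possibly after seeing data. Different choices give different adherent proportions in each arm.

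For diet there is a further problem. On one reading, the adherent label goes to intakes that miss the plan's own fruit and vegetable target and is withheld from an intake that meets it. No other adherent/nonadherent rule is given, so the behaviour component of the primary outcome may rest on these classes.

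**Working it through.** No stated figure has to be reproduced. The check assigns classes value by value under each plausible reading.

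**Diet unit.** Servings per day per week is not a unit. Read per day, 2–4 is 14–28 per week (2 × 7 and 4 × 7); read per week, it is 2–4. The two differ sevenfold.

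**Diet, numbers read as servings eaten per day.** This reading fits the wording of Good. Poor can mean either 'not more than five' or 'below Fair'.

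| Servings/day | Poor = not more than 5 | Poor = below Fair | Within 5–7 target |
|---|---|---|---|
| 0–1 | Poor | Poor | no |
| 2, 3, 4 | Poor and Fair | Fair (adherent) | no |
| 5 | Poor (non-adherent) | no class | yes |
| 6, 7 | Good (adherent) | Good (adherent) | yes |

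Under both versions, 5 servings is never adherent, while 2–4 carries the adherent label. The shortfall of the Fair class from the lower end of the target is 5 − 4 = 1 to 5 − 2 = 3 servings.

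**Diet, numbers read as deviations from advice.** Take Poor as more than 5, Fair as 2–4 and Good as none. Then 1 and 5 deviations have no class.

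**Activity, minutes per week.** Fair's vigorous range is taken as 60–130 min to make a check possible; the text does not establish this.

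| Moderate / vigorous | Poor taken literally (under 150 moderate, or 1 h vigorous) | 'Less than' covers both limbs, joined by 'or' | Both limbs joined by 'and' |
|---|---|---|---|
| 0 / 60 | Poor and Fair | Poor and Fair | Fair |
| 200 / 30 | Fair | Poor and Fair | Fair |
| 260 / 30 | Good | Poor and Good | Good |
| 0 / 140 (not at work) | Poor | Poor | no class |

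The overlap goes only if 'or' is changed to 'and'. Vigorous activity above the range, outside work and with under 150 min moderate, then has no class. Vigorous work is Good with no minutes attached. The 150 min moderate threshold agrees across the adherence section, the Physical activity definition and the secondary outcomes.

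**Why the cut-off matters.** If 2–4 servings counts as adherent, the arm difference equals the difference in the share eating 5 or more plus the difference in the share eating 2–4. The shares below are assumed, not taken from the document, and anyone at exactly 5 is counted as adherent for simplicity. Let 20% of controls and 30% of the intervention arm eat 5 or more, a 10-point difference.
- 2–4 servings in 40% vs 30%: 60% vs 60%, difference 0.
- 40% vs 40%: 60% vs 70%, difference 10 points.
- 30% vs 40%: 50% vs 70%, difference 20 points.

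This shows only that the choice of cut-off can change the arm difference. It forecasts neither size nor direction.

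**The case against.** Several stronger readings are tempting, and the document does not support them.

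- **That these rules define the primary outcome.** This is an inference. The analysis sentence names no outcome, and the primary outcome section does not refer to adherence. The link is plausible because no other dichotomy is given, but it is not stated.
- **That someone eating 2 servings a day is certainly a primary outcome success.** Fair speaks of deviation from advice, and Poor parallels it if the numbers count departures. That reading softens the conflict with the 5–7 target, although it fits Good poorly and still leaves gaps. The section also never names fruit and vegetables; the advice may cover everything under Healthy eating.
- **That the diet classes both overlap and leave a gap.** On the intake reading, the overlap at 2–4 and the gap at 5 come from different meanings of Poor and do not occur together.
- **That the rule contradicts a WHO number.** The document gives no WHO serving figure. The numerical conflict is with the secondary outcome target.
- **That activity Poor plainly includes one hour of vigorous activity.** 'Less than' more naturally covers both limbs. This stands as an objection, but the 'or' still creates overlaps.
- **That self-report biases the result upwards.** Adherence is self-reported by unblinded participants and only one arm receives texts, so differential reporting is possible. Both arms, however, receive the same baseline education and written recommendations, and neither size nor net direction can be derived.
- **That leaving step counts out of the listed outcomes is an error.** The article says "we will measure their achieved steps per week" by smartphone; how these are analysed may sit in the full protocol or analysis plan.

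It is also fair to say that the sample size rests on diabetes development, which is defined by HbA1c or a previous diagnosis with medication. Nothing here affects it.

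**Conclusion.** The point holds as a defect in stated rules rather than as missing detail. No reading tried gives exclusive and exhaustive classes on both scales, and the diet unit and the vigorous range cannot be applied as written. On the intake reading, four whole-number values (2, 3, 4 and 5 servings/day) are in conflict with the plan's own target or left without a class. That conflict depends on reading the numbers as servings eaten; the undefined unit does not, and gaps remain on the deviation reading too. The effect on the arm comparison cannot be quantified from the document. The weight of the defect depends on whether this variable is the behaviour primary outcome, which the protocol should say.

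**What to change.** Reconcile Assessment of interventions and the two adherence sections with the Physical activity definition and the secondary outcomes:

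1. Give each behaviour one mutually exclusive and exhaustive adherent/nonadherent rule in a stated unit.
2. For diet, align the fruit and vegetable component with the plan's own 5–7 servings/day target, and say how the other elements under Healthy eating enter the rule.
3. For activity, use the full Physical activity definition, including its days-per-week condition, and say how vigorous activity and vigorous work are counted.
4. Keep the three-level score as descriptive only, with one name for the middle level.
5. State whether the binary variable is the behaviour component of the primary outcome.

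Reporting the step counts already planned as a supportive objective measure is optional; phone-based counts are imperfect.

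The cost is protocol wording and a derived variable. The adherent proportion may look lower than under the present labels.
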